#### *Safety*

S2.SE9 The proportion of patients eligible to receive PQ who had a serious adverse event (SAE) during treatment.

S2.SE10 The proportion of patients treated with PQ experiencing at least one AESI during treatment.

S2.SE11 The proportion of patients treated with PQ with an AESI related to haemolysis during treatment.

S2.SE12 The proportion of patients treated with PQ with a gastrointestinal AESI during treatment.

S2.SE13 The proportion of patients treated with PQ with AESI related to methaemoglobinaemia during treatment.

S2.SE14 Prevalence of severe anaemia (haemoglobin < 7g/dl) in patients presenting with fever in the Pre-Implementation Survey versus the late Post-implementation Survey (derived from the quantitative surveys).

- Median and distribution of haemoglobin concentrations will also be presented for each survey

*Effectiveness*

- S2.SE15 The monthly incidence of confirmed symptomatic *P. vivax* malaria episodes (mono-infection or mixed) in the Pre-Implementation (12 months) versus Post-Implementation Stage 2 ((a) level change in 6 months post implementation (i.e. period between 6 and 12 months post-implementation), (b) change in trend of incidence immediately post-implementation (i.e. entire 12 month period post-implementation)).
- S2.SE16 Prevalence of *P. vivax* parasitaemia in patients presenting with fever in the Pre-Implementation Survey versus the Post-Implementation Survey during Stage 2 (derived from the quantitative surveys).
- S2.SE17 Cumulative risk of representation to the same health facility with symptomatic *P. vivax* malaria within 6 months in the Pre- and Post-Implementation Stages.
- S2.SE18 Cumulative risk of representation to the same health facility with symptomatic *P. vivax* malaria within 6 months in the Post-Implementation Stage for patients enrolled and not enrolled in SCOPE.

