### 6.2. Stage 2 – Large-scale implementation and feasibility study

The primary analysis of the endpoints in Stage 2 will include all patients enrolled across the 10 health facilities in Indonesia and Papua New Guinea from the start of the pre-implementation period to the end of the post-implementation period (estimated to be about 16,300 patients). Before versus after analyses of the prevalence of asexual *P. vivax* parasitaemia and severe anaemia from the cross-sectional surveys will be done on the full aggregated dataset of all patients enrolled in the surveys across the 10 study sites (aiming for 200 patients each health facility for each survey = 4,000 patients total).

Secondary analyses of patient-related study outcomes will be conducted for the following pre-specified subgroups:

- Patients from Indonesia & Papua New Guinea
- Patients from PNG, Indonesian Papua and Sumatra
- Study site
- Ethnic group
- Patients with G6PD activity >70%, ≥30% to ≤70% and <30%
- Patients prescribed PQ7, PQ14 and PQ8W
- Patients aged <5 years, 5-15 years and >15 years
- Males and females

All of the health facilities in the study are already collecting *P. vivax* malaria incidence data.

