The model will include time (month) as a continuous variable, a binary variable for the implementation intervention (see (a) and (b) above), an interaction between elapsed time (since implementation) and the implementation, seasonal variation in malaria (captured using splines), adjusted for potential time-varying confounding variables including large scale malaria control activities outside of the SCOPE study and unexpected antimalarial stock outages, and allowing for a random effect for intercept to account for clustering by health facility site (Turner SL et al. 2021).

For the effectiveness outcome S2.SE15, monthly incidence of symptomatic *P. vivax* malaria will be calculated using clinic catchment populations provided by health facilities (or if not available, the most recent census). Incidence rate ratios (IRRs) (95% CIs) for the intervention effect will be estimated from a negative binomial regression model fitted to the monthly aggregated data.

**Figure 2.** Example impact model for the implementation package on the effectiveness outcome measure S2.SE15 (incidence of symptomatic *P. vivax* malaria infections). An impact model with an immediate change in level and slope. While immediate level change is allowed to occur in this model at the time of implementation, the estimand of interest with regards to level change will be calculated 6 months after implementation (at 12 months) relative to the implementation timepoint (at 6 months).

[figure not shown]

For comparison of outcomes S2.SE16 (the proportion of febrile patients with asexual *P. vivax* parasitaemia by microscopy) and S2.SE14 (the proportion of patients with severe anaemia (haemoglobin < 7 g/dl), determined from cross-sectional surveys in the pre- and post-implementation periods), prevalence ratios (95% CIs) for the intervention effect will be estimated from log-binomial regression models, and if there are convergence issues, Poisson regression with robust variance will be performed (Barros AJD & Hirakata VN 2003).

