### Clustering

The relevant hierarchy of observations is that observations over time are clustered within health-facility. This clustering will be explored in analyses of the effectiveness outcomes using either random effects or robust standard errors for clustering by health facility.

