### **Heterogeneity**

The mixed effects models allow for some heterogeneity in slope and intercept at the health facility level. A visual assessment of heterogeneity of intervention effect according to site characteristics will be performed.

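### The SAP does not ensure that the survey prevalence ratios allow for facility-by-period variation: S2.SE14 has no clustering provision, and S2.SE16 has only an open choice

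*SAP*

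**What the plan says.** Section 9.2 of the SAP gives one model for both survey outcomes: "prevalence ratios (95% CIs) for the intervention effect will be estimated from log-binomial regression models". The same sentence adds a fallback to Poisson regression with a robust variance, should the first model fail to converge. It names no facility term and does not say at what level the robust variance is computed. Section 6.2 puts the surveys into one dataset pooled over the ten sites, "aiming for 200 patients each health facility for each survey = 4,000 patients total".

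The Clustering paragraph in the same section reads: "This clustering will be explored in analyses of the effectiveness outcomes using either random effects or robust standard errors for clustering by health facility".

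Section 2.2.2 places the two endpoints under different subheadings:

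- S2.SE14, under Safety: "Prevalence of severe anaemia (haemoglobin < 7g/dl) in patients presenting with fever in the Pre-Implementation Survey versus the late Post-implementation Survey".
- S2.SE16, under Effectiveness: prevalence of *P. vivax* "parasitaemia in patients presenting with fever in the Pre-Implementation Survey versus the Post-Implementation Survey during Stage 2".

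Section 9.3, Heterogeneity, adds: "The mixed effects models allow for some heterogeneity in slope and intercept at the health facility level". Section 9.2 names a facility random intercept for the incidence model (S2.SE15) and a facility shared frailty for the recurrence model (S2.SE17). It names neither for the survey models.

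**The concern.** Each facility is surveyed once midway through pre-implementation and once in the final six months of post-implementation (section 3.1). A local shift between those two dates therefore enters the before-after ratio directly. Equal numbers per site cancel a stable difference in level between facilities, but not a difference between facilities in how much prevalence changed.

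The SAP itself gives reasons to expect such differences. Section 7 records stock outages and outside control activities by site and month. Section 9.3 plans a visual check of heterogeneity of effect by site. Table 1 shows annual *P. vivax* episodes from 412 to 4,937 per clinic. If this variation is present and left out, the interval treats 4,000 patients as independent, and a change driven by a few facilities can look more certain than it is.

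**Working it through.** **Inputs from the SAP.** Ten facilities, 200 patients per facility per survey, two surveys: 10 × 200 × 2 = 4,000, which reproduces the total in section 6.2 (2,000 per survey). The SAP states no prevalence, precision or power for either survey endpoint, so there is no other figure to reproduce.

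**Assumptions.** Prevalence *p*, and τ, the between-facility SD of the facility-specific log prevalence ratio. The SAP gives neither for the surveys.

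**Formulas.**

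- Pooled SE of the log ratio: SE₀ = √[2(1−p)/(2000p)]
- SE with facility-by-period variation: SE₁ = √(SE₀² + τ²/10)
- Coverage of the pooled 95% interval: 2Φ(1.96·SE₀/SE₁) − 1

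| Endpoint | p | τ | SE₀² | τ²/10 | SE₀ | SE₁ | Coverage |
|---|---|---|---|---|---|---|---|
| S2.SE16 | 20% | 0.2 | 0.004 | 0.004 | 0.063 | 0.089 | 83% |
| S2.SE16 | 20% | 0.3 | 0.004 | 0.009 | 0.063 | 0.114 | 72% |
| S2.SE14 | 1% | 0.3 | 0.099 | 0.009 | 0.315 | 0.329 | 94% |
| S2.SE14 | 2% | 0.5 | 0.049 | 0.025 | 0.221 | 0.272 | 89% |

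**Second parameterisation.** Let ICC be the intra-facility correlation, and CAC the share of between-facility variance that is stable across the two surveys. The ratio of true to pooled variance is 1 − ICC + 200·ICC·(1 − CAC). The assumed ICC range is 0.01 to 0.1. The upper value is borrowed from the superseded incidence simulation in section 4.2.2, since the SAP gives none for the surveys.

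- CAC = 1 (facility effects stable): SE ratio 0.95 to 0.99, so the pooled interval is not too narrow.
- CAC 0.9 to 0.5: SE ratio 1.09 to 1.41 at ICC 0.01, 1.40 to 2.44 at ICC 0.05, and 1.70 to 3.30 at ICC 0.1.
- Example at 15% prevalence, ICC 0.1, CAC 0.8: variance ratio 0.9 + 4 = 4.9, SE ratio 2.21. The 95% limits go from the ratio ×/÷ 1.16 to ×/÷ 1.39.

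The two scales can be linked by τ = SE₀·√[10(variance ratio − 1)]. At 15% prevalence SE₀ = 0.075. With CAC 0.8, ICC 0.01, 0.05 and 0.1 then imply τ of about 0.15, 0.33 and 0.47. The range 0.2 to 0.3 used for S2.SE16 sits inside that span.

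**Simulated coverage** of nominal 95% intervals under no effect (ten facilities, 200 per survey, prevalence 5% to 30%, 1,500 runs per scenario):

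| ICC, CAC | Pooled log-binomial | Facility intercept only (approximate) |
|---|---|---|
| 0.1, 1.0 | 96% | about 95% (at 15% and 30% prevalence) |
| 0.01, 0.8 | 90–91% | 90–91% |
| 0.05, 0.8 | 70–74% | 69–73% |
| 0.1, 0.8 | 58–59% | 55–57% |
| 0.1, 0.5 | 43–45% | 41–43% |

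Over the scenarios with CAC below 1, facility-clustered robust errors covered 84–92% with normal quantiles and 89–95% with t on 9 df. So the two options in the Clustering paragraph are not interchangeable for this design. The lowest simulated prevalence was 5%, so the rare-event case for severe anaemia rests on the formula alone.

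**The case against.** The strongest reply is that S2.SE16 is already provided for. It is an effectiveness endpoint, the Clustering paragraph reaches it, and facility-clustered robust errors, the main remedy here, are one of the two options named. That stands. A reader might infer from the log-binomial sentence that the SAP ignores clustering for both outcomes, and the document does not support this for S2.SE16. What remains there is an undertaking to explore rather than a commitment, an unresolved choice between methods that behave differently, and no small-sample correction.

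A reader might also infer that the intervals are too narrow as a matter of fact. That is not supported either. With stable facility effects the pooled interval covers 96% in simulation, and the SAP gives no survey prevalence, ICC or between-facility SD from which to say otherwise.

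It can be said that random effects need not mean an intercept alone, and that section 9.3 speaks of heterogeneity in slope. But that sentence concerns the mixed effects models, and the survey models are not named as such.

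Finally, the large loss and the clear gap fall on different endpoints. For S2.SE14 most of the uncertainty comes from patients, not facilities: 0.099/0.108 = 92% of the variance at 1% prevalence with SD 0.3, and 0.049/0.074 = 66% at 2% with SD 0.5. This stands, and it limits the consequence for severe anaemia.

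**Conclusion.** The point holds as a gap in specification. For S2.SE14 no clustering provision applies as worded. For S2.SE16 a provision applies, but an analyst could follow it with a random intercept and gain almost nothing, or with uncorrected robust errors and still under-cover.

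The size is conditional on the pre-to-post change differing between facilities, and on assumed values: coverage of about 83% to 72% for a pooled S2.SE16 interval, and a modest loss, to about 94% to 89%, for S2.SE14. Both are secondary endpoints. The primary endpoint S2.PE1 is not affected. The choice should be fixed before the survey comparison is made.

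**What to change.** In the Clustering paragraph of section 9.2, add S2.SE14 to the outcomes covered. For both S2.SE14 and S2.SE16, replace the undertaking to explore with a commitment: prevalence ratios from the log-binomial or modified Poisson model, with robust standard errors clustered by health facility and a small-sample correction (t, 9 df). State that the robust variance in the Poisson fallback is also clustered by facility.

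Do not rely on a random intercept alone. Do not make a facility-by-period random effect the main method for S2.SE14: at 1% to 2% prevalence, 200 patients give only 2 to 4 events per facility and survey, and such a term would be poorly estimated.

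The cost is a change of wording and somewhat wider intervals. No new data are needed.

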#### 4.2.1 Revised and corrected Stage 2 power and precision calculations

Assumptions underlying the following Stage 2 power calculations include the following:

1. 5% of patients are ineligible for the intervention package (pregnancy, lactation, severe malaria, age <6m (Indonesia) or <1 yr (PNG)).
2. The impact on the risk and rate of infection will be the same across different endemic sites.
3. The mean baseline risk of *P. vivax* recurrence at 6 months is 20%
4. Loss to follow-up in both groups is 10%
5. Alpha = 0.05

During the 12-month pre-implementation period, a total of **17,160** patients with *P. vivax* (mono or mixed infections) presented to the ten study clinics (see Table 1). Assuming 5% of patients are ineligible for enrolment due to pregnancy, lactation or age under 6 months (Indonesia) or 12 months (PNG), this gives an estimated maximum number of patients eligible for recruitment into Stage 2 of **16,300**.

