| 0.5                                                               | 8,150                                   | 135.8                                                           | 12.22                                  | 123.58                                                            | 63.2%                                         |

**Example STATA code:** power pairedm 135.8 111.36, sddiff(15) n(10) alpha(0.05).

Based on previous estimates, 60% of cases of *P. vivax* malaria seen at each clinic are due to relapse and therefore preventable with improved radical cure. We predict the intervention package will reduce the individual risk of relapse by 30%. With anticipated recruitment of 70% of eligible patients, the total predicted sample size in Stage 2 would fall to **11,410** patients receiving primaquine over 12 months of enrolment. Based on this lower predicted enrolment and using the assumptions as above, the predicted absolute reduction in incidence at each clinic would be 17.11 cases per month  $((135.8 \times 0.6) \times 0.3 \times 0.7)$  and resultant power to detect this difference would be **89.3%**.

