### **S2.SE17 - Reduction in individual risk of recurrence**

The power estimates for detecting a reduction in the individual risk of recurrence of *P. vivax* within 6 months from an anticipated study enrolment of **11,410 patients** are presented in Table 3. The number of patients included in the pre-implementation and implementation stages are assumed to be equal (ie a total of 22,820 patients pre and post implementation).

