**Table 3 – Power to detect reduction in the risk of recurrence**

| Proportion of eligible P. vivax malaria patients recruited | Eligible patients over 12 months period | 30% Risk Reduction (HR 0.7) | 20% Risk Reduction (HR 0.8) | 10% Risk Reduction (HR 0.9) |
|-------------------------------------------------------------------|-----------------------------------------|-----------------------------|-----------------------------|-----------------------------|
| 1                                                                 | 16,300                                  | 100%                        | 100%                        | 98%                         |
| 0.9                                                               | 14,670                                  | 100%                        | 100%                        | 97%                         |
| 0.8                                                               | 13,040                                  | 100%                        | 100%                        | 95%                         |
| 0.7                                                               | 11,410                                  | 100%                        | 100%                        | 92%                  |
| 0.6                                                               | 9,780                                   | 100%                        | 100%                        | 88%                         |
| 0.5                                                               | 8,150                                   | 100%                        | 100%                        | 82%                         |

**Example STATA code:** artsurv, edf0(0.2) hr (1,0.7) fp(1) n(22,820) alpha(0.05) nperiod(1) tunit(2) lg(1 2) ldf(0.1;0.1).

A sample size of 11,410 (70% eligible patients) would provide **92% power** to detect a minimum 10% reduction in risk of recurrence and 100% power to detect a 30% reduction in risk of recurrence.

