Individual patient data on the risk of representation with vivax malaria within 6 months to the same health facility site (S2.SE17) will be analysed using survival analysis and visualised with Kaplan-Meier curves. The risk of recurrence will be determined for all patients eligible for PQ treatment and compared between the pre- and post-implementation stages. Multivariable Cox proportional hazards regression will be used to compare these same groups, controlling for age, sex, body weight, calendar time (month), seasonality (captured using splines) and shared frailty of health facility. The validity of the proportional hazards assumption will be assessed visually using Schoenfeld residuals and stratified analyses will be conducted where the assumption is violated.

For S2.EE1, the number and proportion (and 95% Confidence Interval) of patients observed to have a >25% reduction in haemoglobin to a concentration below 7 g/dl will be computed by treatment arm (PQ7, PQ14, PQ8w), and described in summary tables.

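### Table 3's 92% power for S2.SE17 is computed for enrolled patients at full effect, but section 9.2 analyses all PQ-eligible patients; on that population it is about 80% if non-enrolled patients gain nothing

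*SAP*

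**What the plan says.** **Analysis.** Section 9.2 defines the S2.SE17 comparison: "The risk of recurrence will be determined for all patients eligible for PQ treatment and compared between the pre- and post-implementation stages". Enrolment is not mentioned. The parallel rule for S2.SE18 in section 11 does name SCOPE and non-SCOPE patients.

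**Power.** Section 4.2.1 bases S2.SE17 on an anticipated enrolment of 11,410. It adds: "The number of patients included in the pre-implementation and implementation stages are assumed to be equal", which gives 22,820 in total. Below Table 3 it claims 92% power "to detect a minimum 10% reduction in risk of recurrence and 100% power to detect a 30% reduction in risk of recurrence". Every recruitment row uses the same hazard ratios (0.7, 0.8, 0.9), and only the number of patients falls.

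**Treatment of the shortfall for S2.SE15.** The text under Table 2 begins "With anticipated recruitment of 70% of eligible patients, the total predicted sample size in Stage 2 would fall to" 11,410, then multiplies the predicted incidence reduction by 0.7: 135.8 × 0.6 × 0.3 × 0.7 = 17.11 cases per month.

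**Analysis set.** Section 6.2 says: "The primary analysis of the endpoints in Stage 2 will include all patients enrolled across the 10 health facilities". It runs this from the start of pre-implementation to the end of post-implementation and puts the number at about 16,300.

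**The concern.** If all eligible patients are analysed, weak recruitment does not shrink the sample. It shrinks the effect, because the non-enrolled part of the post-implementation group does not receive the package. Table 3 does the reverse: it cuts the sample and keeps the effect. Two neighbouring tables therefore handle the same shortfall in opposite ways.

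The section 6.2 figure does not settle the matter. About 16,300 over both periods matches neither 22,820 (11,410 per period) nor 32,600 (16,300 per period). The package is not on offer before implementation, so the documents also identify no enrolled pre-implementation group that would supply a matching 11,410.

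Two things are at stake. One is a power claim that the SAP prints in bold. The other is the estimand: including or leaving out non-enrolled patients changes S2.SE17 from a programme effect, diluted by uptake, to an effect among recipients, and the SAP should not leave that choice open.

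**Working it through.** **Inputs (section 4.2.1).** "The mean baseline risk of *P. vivax* recurrence at 6 months is 20" per cent; "Loss to follow-up in both groups is 10" per cent; alpha 0.05, taken as two-sided; 16,300 eligible patients per 12 months; 11,410 enrolled at 70% recruitment.

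**Formulas.** Post-implementation risk among recipients: p1 = 1 − 0.8^HR. Events: D = n per period × 0.95 × (0.20 + p1), where 0.95 spreads the 10% loss over follow-up. Power = Φ(|ln HR| × √D / 2 − 1.96).

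**Step 1: reproduce the 92%.**
- p1 = 1 − 0.8^0.9 = 0.18195
- D = 11,410 × 0.95 × 0.38195 = 4,140
- |ln 0.9| × √4,140 / 2 = 3.39, and 3.39 − 1.96 = 1.43, so power is 92.4%

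Other methods and ways of handling the loss give 90.8% to 93.6%. The plan's figure is confirmed on its own inputs.

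**Step 2: the section 9.2 population.** Take 16,300 per period, with 70% of the post-implementation group at HR 0.9 and 30% at the 20% baseline risk (an assumption).
- Post-implementation risk = 0.7 × 0.18195 + 0.3 × 0.20 = 0.18736
- Whole-group HR = ln(1 − 0.18736) / ln(0.8) = 0.930
- D = 16,300 × 0.95 × 0.38736 = 5,998
- |ln 0.930| × √5,998 / 2 = 2.82, and 2.82 − 1.96 = 0.86, so power is 80.5%

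The range over ways of handling the loss is 78.2% to 82.5%.

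**Step 3: all recruitment rows, 10% reduction among recipients.**

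| Recruited | Table 3 | Reproduced | All eligible, effect diluted |
|---|---|---|---|
| 100% | 98% | 98.2% | 98.2% |
| 90% | 97% | 97.0% | 95.3% |
| 80% | 95% | 95.2% | 89.8% |
| 70% | 92% | 92.4% | 80.5% |
| 60% | 88% | 88.1% | 67.5% |
| 50% | 82% | 81.7% | 51.9% |

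**Step 4: larger effects at 70% recruitment.** A 20% reduction among recipients gives a whole-group HR of 0.859, and a 30% reduction gives 0.788. Power is above 99.9% in both cases.

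**Step 5: relax the assumption in step 2.** Give the non-enrolled 30% some benefit, at 70% recruitment and HR 0.9 among recipients:
- non-enrolled HR 0.98: whole-group HR 0.924, power 86.5%
- non-enrolled HR 0.95: whole-group HR 0.915, power 93%
- non-enrolled HR 0.90: whole-group HR 0.90, power 98%

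**Step 6: a mixed reading.** Comparing 11,410 enrolled post-implementation patients with 16,300 eligible pre-implementation patients at HR 0.9 gives 95% to 96%. Among the readings set by how the population is defined, only 11,410 against 11,410 at full effect yields the plan's 92%.

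**The case against.** **The expected effect is safe.** The plan predicts a 30% reduction in individual relapse risk, and power there is untouched. On the step 2 model, 90% power at 70% recruitment needs a reduction among recipients of about 11.5%, so the practical shift is small. This stands. A reader might infer that S2.SE17 is underpowered, but the SAP's figures do not support that at the effect it expects.

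**Table 3 does not say whose hazard ratio it is.** If HR 0.9 is meant as the contrast between all eligible patients in the two periods, power is 98% and 92% is conservative. That is fair, and it is why the HR needs a label. It does not rescue the 92%.

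**The 80% rests on an assumption.** The SAP gives no recurrence risk for non-enrolled patients after implementation, and some benefit at the same facilities is possible. The 80% is therefore conditional and belongs with the range in step 5.

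**Both calculations are idealised.** Neither allows for clustering by facility or the calendar-time adjustment in section 9.2. Table 1 counts episodes, so 16,300 may overstate the number of distinct patients. These limits apply to 92% and 80% alike.

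**Section 6.2 may be loose general wording.** It covers all Stage 2 endpoints, whereas section 9.2 is the specific rule for S2.SE17. That is probably the right reading, and one sentence would make it explicit.

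**Low enrolment was recognised.** Section 11 adds S2.SE18 for this reason. But that is an exploratory comparison of enrolled and non-enrolled patients, and it does not correct Table 3.

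**A tempting step to avoid.** Section 10 says that patients without a malaria card tend to be more transient and to seek care differently. A reader might take this as evidence of selection by enrolment in S2.SE17. It concerns Indonesian patients in a sensitivity analysis of S2.SE18, and it says nothing about consent or enrolment in S2.SE17.

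**Conclusion.** The point holds as a mismatch between the population that was powered and the population to be analysed. The 92% is not a calculation error; it belongs to a comparison that section 9.2 does not make. For a 10% reduction among recipients at 70% recruitment, the figure on the section 9.2 population is about 80% if non-enrolled patients stay at the 20% baseline risk, and it approaches 98% if they benefit as much as recipients. The gap widens as recruitment falls. The practical loss is confined to small effects. The more lasting reason to act is that sections 4.2.1, 6.2 and 9.2 describe three different populations for the individual-level effectiveness endpoint.

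**What to change.** 1. State in section 9.2 that S2.SE17 uses all PQ-eligible *P. vivax* patients in both periods, whether or not enrolled, and exempt S2.SE17 from the enrolled wording in section 6.2.
2. Recompute Table 3 with 16,300 per period and the effect scaled by the recruited share, as Table 2 does. Label the hazard ratio as the effect among recipients.
3. For a 10% reduction among recipients, replace 92% with about 80% at 70% recruitment, and give about 67% at 60% and about 52% at 50%. State the assumption that non-enrolled patients keep the 20% baseline risk, and that power rises towards 98% at 70% recruitment if they benefit equally.
4. Note that power stays above 99.9% for 20% and 30% reductions at 70% recruitment, and that clustering and calendar-time adjustment are not allowed for.

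The cost is SAP wording and one recomputed table. The stated power for the smallest effect becomes less favourable. No extra patients or data are needed.
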